**Fig. 3 Fig3:**
[figure not shown]
*Andilaye* Trial flow diagram

### Implementation

The *Andilaye* intervention is being implemented in collaboration with the *Woreda* Health Offices, HEWs, WDALs, and other community change agents in the 25 *kebeles* randomly selected to the *Andilaye* intervention arm. While allocation occurred at the *kebele* level, intervention activities and data collection occur in one to two sentinel *gotts* per *kebele*, purposively selected to minimize spillover. The counterfactual, or control arm, includes households from *gotts* within randomly selected *kebeles* receiving the FMoH’s standard of care CLTSH programming. As this study is operating in an area where CLTSH is being rolled out nationally, we are not interfering with established CLTSH roll-out and implementation protocols. While we cannot be sure that our control communities will not receive further CLTSH interventions during the course of the trial, any such further implementation of the current CLTSH interventions would only bias effect estimates toward the null.

### Data collection and data management methods

Survey instruments administered at baseline and follow-up data collection rounds (midline and endline) consist of several modules aimed at collecting data on key outcome indicators through reports from respondents and other household members (Additional file 5: Table S3 and Additional file 6: Table S4). When developing these tools, we pulled from a reserve of existing WASH indicators, and leveraged formative research data to contextually adapt survey prompts and answer choices. To the greatest extent possible, we included validated metrics for assessment. Prior to enumerator training, the survey instrument was translated into Amharic, and back-translated by two independent Amharic speakers. The study team discussed and reconciled any discrepancies noted between the intended English prompts and the Amharic translations (identified via the back-translations). In order to ensure face validity, the vast majority of the survey instrument was tested via cognitive interviews. Through the use of this qualitative method, which included ‘think-aloud’ and verbal probing techniques, we obtained feedback from formative research households about the meaning, comprehensiveness, and appropriateness of survey prompts and their related answer choices. Once the Amharic version of the tool was complete, four enumerators were trained on the tool, and administered it during a week-long field pilot in targeted formative research communities. At the end of each day of piloting, the team discussed issues related to respondent comprehension of survey prompts and answer choices, survey logic and skip patterns, and suggested revisions were incorporated, as appropriate. At the end of the piloting period, key data were checked and analyzed, and further modifications were made to the tool prior to finalizing the instrument and supervisor and enumerator trainings. Select finalized survey prompts and answer choices can be found in Additional file 6: Table S4.

The *Andilaye* Trial survey is administered electronically on password-protected mobile phones by enumerators and field supervisors (e.g., completing validation surveys) to improve accuracy of data entry and enable immediate review of results. Data is stored securely using the freely available Open Data Kit (http://opendatakit.org/). Logic, range, and consistency checks were incorporated into the electronic data collection file to further improve data quality and minimize data entry errors. To ensure data quality, the supervisory team, comprised of faculty and staff from Emory University and Emory Ethiopia (a university-derived non-governmental organization in Ethiopia), will coordinate and supervise data collection along with field supervisors. Field supervisors independently assess all objective measures (simultaneous to, but independent of enumerator assessment for validation surveys) at 10% of households in each study *kebele*. Supervisor and enumerator data captured from this sub-set of households will be compared to determine inter-rater reliability of related metrics.

All enumerators and field supervisors are external evaluators who are hired for discrete data collection activities (i.e., baseline, midline, endline, quarterly monitoring). Study staff will not disclose study cluster treatment allocation to field supervisors or enumerators. However, given the nature of the intervention, they may observe intervention materials in *Andilaye* intervention clusters, which may signal treatment allocation.

We will measure and track individual, household, and community-level changes in key outcomes over multiple time points (i.e., baseline, midline, and endline). Households enrolled in the study are lost to follow-up if: (1) consent to participate in our follow-up survey was refused, (2) the entire household moved out of the study *kebele*, or (3) no child aged 1–10 years (at midline) or aged 1–11 years (at endline) resides in the household any longer. Households with no eligible respondent available after three attempts during midline data collection will continue to be enrolled in the study, and will be visited for subsequent quarterly monitoring and endline data collection. A sub-set of key data points will be collected during quarterly monitoring, however, we will seek to minimize reactivity by only engaging half of all households in each cluster per quarter, such that we visit each household for monitoring only once per annum.

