### Study outcomes and measures

Primary outcomes of interest include:Sustainability of WASH-related behaviors, as measured through the proportion of individuals and households consistently practicing improved targeted WASH behaviors, including: (1) sanitation, (2) personal hygiene, and (3) household environmental sanitation, more specifically, the 11 constituent practices identified above; andMental well-being, as measured through standardized mental well-being scale scores generated via the administration of the WHO-5 [40] and Hopkins Symptom Checklist (HSCL) [41].

Secondary outcomes of interest include:Short-term behavioral outcomes, measured as the proportion of households with improved (private or shared) latrines and washing facilities that are functional and available for use; proportion of households using functional latrines and washing facilities; proportion of households with all members exclusively using a latrine for defecation; proportion of households disposing of child feces in an improved latrine; proportion of households with all children in the household with a clean face and hands;Intermediate behavioral antecedents, measured as the proportion of households with improved knowledge regarding the implications of improved WASH practices (i.e., perceptions regarding negative externalities); proportion of households that indicate positive attitudes, perceptions toward improved sanitation and good hygiene practices; change in normative expectations related to open defecation, exclusive latrine use for defecation, and personal hygiene practices;Diarrhea period prevalence, as measured through caregiver self-report;Sanitation insecurity, as measured through changes in sanitation insecurity scale scores [19];Collective efficacy measures, as measured through changes in collective efficacy scale scores [42]; andWater insecurity, as measured through changes in water insecurity scale scores [43].

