We employed a structured sampling strategy to randomly select eligible *kebeles* within the sampling frame. The primary sampling unit for this study was the *kebele*. The secondary sampling unit for this study was the household; specifically, any household residing in a targeted, sentinel village (*gott*) within a randomly selected study *kebele*. While we randomly selected eligible study clusters (i.e., *kebeles*), we purposively selected *gott(s)*, from which we randomly selected study households. We utilized a ‘fried egg’ [50] approach to purposively select one to two *gotts* that were either situated in or near the center of the *kebele* (if there were centric *gotts*) or were not adjacent to any other study *kebele* (in the event there are no centric *gotts*). This approach minimized spill-over of intervention effects and other externalities associated with the research between intervention and control clusters, especially those adjacent to each other. The number of targeted *gotts* depended only on the number of eligible households identified in *gott* census books. Study household inclusion criteria for the *Andilaye* Trial included any household randomly selected from the *gott* census book residing in the target *gott*(s) that: (1) had at least one child aged 1–9 years at baseline (i.e., the study’s index children) and consented to allowing study staff to observe the children, specifically their faces and hands, and (2) provided consent to participate in the study, with at least one adult household member consenting to serve as the primary survey respondent.

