Recruitment took place within the home compounds during baseline data collection. Enumerators contacted adult members of the household; they explained the purpose of the visit, the purpose of the study, and asked the respondent if s/he would be willing to consent to participate in the study using a structured consent form (Additional file 4). Enumerators assessed household level eligibility by asking potential survey respondents a series of questions that lead to a determination of eligibility, and enrolled eligible and consenting households into the trial. During the consent process, enumerators informed respondents that they had the right to choose not to participate in the study, the right to refuse to answer any question, and the right to stop the survey for any reason at any point in time. Enumerators targeted primary survey respondents, based on the following order of priority: (1) the primary female caregiver of the index child, (2) any female household member who serves as a caregiver, (3) any male household member who serves as a caregiver, and (4) any household member over 18 year of age. If households were absent after three visits, no eligible adult respondent was available or refused to consent, or upon further conversation with the household, it became apparent that it was not eligible (e.g., no child aged 1–9 years), the enumerator recorded the information and notified the field supervisor prior to replacing that household with the next randomly selected household on the study roster. Of 1691 surveys initiated during baseline, 1589 (94%) households met all inclusion criteria and were enrolled into the study – 89 households more than the targeted sample size. Targeted households that did not meet inclusion criteria were excluded for the following reasons: 81 households did not have a household member between 1 and 9 years of age, 17 households had no eligible respondent available, three surveys were initiated but not fully completed, and one household did not consent to participate.

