### Random allocation

Following baseline data collection, we used a stratified random design to assign study *kebeles* to either the *Andilaye* intervention or control arm (CLTSH). Within each stratum (*woreda*), researchers from Emory University in Atlanta, USA used a computer-based random number generator to generate a random number between zero and one for each *kebele* cluster, and then placed the clusters in ascending order by their randomly generated numbers. We then partitioned the communities within each *woreda* into two equal sizes, assigning the first half of *kebeles* to the intervention arm and the second half to the control arm. We used replacement re-randomization [51] to secure balance across three key variables (latrine coverage, washing station with soap coverage, and head of household education), as indicated by our baseline survey. CRTs, particularly trials with a small number of clusters, often have individual-level imbalances between study arms. Therefore, we established a priori that the intervention and control mean values for these three variables should be within two standard deviations of the overall mean for these variables. The randomization process described above was repeated (twice) until these variables were balanced according to that *a prior* criterion. Results from our equivalence analyses indicated balance in the number of previously triggered and ODF certified *kebeles*, between study arms, with 20 triggered and ODF *kebeles* in the intervention arm (80%, 20 of 25 study clusters) and 19 in the control arm (76%, 19 of 25 study clusters). Figure 3 provides further details in a flow diagram.

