### Analytical methods

The primary method of analysis for all primary and secondary outcomes will follow an “intention-to-treat” analysis, which compares the intervention arm to the control arm, without regard to intervention fidelity or compliance. For binary outcomes, such as our targeted WASH behaviors, we will preferentially use log-linear binomial regression models. For continuous outcomes, such as the mental well-being scale scores, we will use linear regression models. All models will include an intervention variable as a fixed effect, and account for the stratified design through the inclusion of the *woreda* indicator variable [52], and incorporate generalized estimating equations with robust standard errors to account for the clustering of observations within *kebeles*.

The majority of our primary and secondary outcomes (shown in Additional file 5: Table S3) are binary variables, and for these we will preferentially use log-linear binomial models; however, log-linear binomial models are known to have difficulty converging, and so we may instead use modified Poisson regression if we encounter problems with convergence [53]. There is often interest in showing an absolute measure along with a relative measure (e.g., a prevalence ratio), so we will also present prevalence differences. We will use the same models as described above (e.g., log-linear binomial models), but use post-estimation commands to estimate the average marginal effects.

Given no imbalances were detected between study arms at baseline for any of the primary variables of interest (Table 1), we will not need to perform supplementary analyses, as outlined in our pre-analysis plan, to control for the baseline levels of these imbalanced variables in more fully adjusted models. For many of our outcomes, there is interest in determining the impact of the intervention across various sub-groups, such as sex, follow-up round (once multiple rounds of collection are completed), exposure to previous triggering, and modifiers such as water and sanitation insecurity. For select key outcomes, we will use interaction terms and/or stratification, and we will present the impact of the intervention at each level of the sub-group variable (e.g., separately for boys and girls).

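### Counting a household as lost once no child in the age window lives there is an avoidable post-randomization exclusion from adult and household outcomes

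*Protocol article*

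**What the plan says.** Data collection and data management methods lists three reasons for loss to follow-up: refusal, the whole household leaving the kebele, and that "no child aged 1–10 years (at midline) or aged 1–11 years (at endline) resides in the household any longer". The next sentence treats another case differently: a household where no eligible respondent can be found at midline stays enrolled and is visited again.

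Eligibility criteria required that a household "had at least one child aged 1–9 years at baseline". Random allocation places the assignment after enrolment: "Following baseline data collection, we used a stratified random design to assign study" kebeles to the two arms.

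Study outcomes and measures names two primary outcomes. One is the "proportion of individuals and households consistently practicing improved targeted WASH behaviors". The other is mental well-being, "as measured through standardized mental well-being scale scores generated via the administration of the WHO-5" and the HSCL. Analytical methods applies intention-to-treat to all primary and secondary outcomes and describes it as an analysis that "compares the intervention arm to the control arm, without regard to intervention fidelity or compliance".

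**The concern.** The third condition is tied to the presence of a child, but the outcome on which the trial was powered is the adult respondent's own mental well-being. A household that is present, reachable and willing is dropped from every outcome because some outcomes need a child. A household that could not be reached at midline is kept.

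A child's death or departure is the kind of event that can affect a caregiver's mental well-being, and 84.6% of baseline respondents were the index child's mother (Table 1). The exclusion may therefore be related to a primary outcome. It could also depend on arm: the intervention is meant to contribute to infectious disease control (Trial design), and the Background ties nearly 20% of under-5 deaths in low-income settings to diarrhea. An analysis plan can choose how to handle missing values, but it cannot recover interviews that were never held.

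**Working it through.** **1. Which outcomes need a child?**
- No child needed: WHO-5 and HSCL, which respondents answer about themselves (Table 1 footnotes). At recruitment the respondent did not have to be a caregiver; the last fallback was "any household member over 18 year of age".
- No child needed: latrine access, the respondent's place of defecation, washing stations, the respondent's handwashing, and animal waste in the compound (Table 1).
- Child needed: face and hand observations, disposal of child feces, diarrhea in the index child.

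Table 1 already uses outcome-specific denominators: 961 for child feces disposal against 1589 for the respondent's place of defecation. Restricting only the child outcomes would follow existing practice.

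**2. How often would ageing alone trigger the rule?** The upper age limit is 9 at baseline, 10 at midline and 11 at endline, one more year per round. The Timeline gives March to April 2017 for baseline and March to May 2019 for endline, at most 27 months. To reach 12 by endline, a child must have been at least 12 years minus 27 months, or 9 years 9 months, at baseline. The index child is the youngest aged 1–9, so the household must also have no younger child who has since entered the window. Ageing-out is therefore an edge case, and death or departure is the main trigger.

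**3. The plan's own figures.** The target of 30 households per kebele reproduces as 25 × 1.20 = 30, and 30 × 50 = 1500. The 20% allowance is not split by reason.

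For the detectable difference the inputs are poor well-being 33.2%, ICC 0.026, 25 clusters per arm, and 1589/50 = 31.78 households per cluster. A two-sided 5% level is assumed because none is stated.
- Design effect = 1 + (31.78 − 1) × 0.026 = 1.800
- Effective n per arm = 25 × 31.78 / 1.800 = 441.3
- Solve d = [1.96√(2p̄(1 − p̄)) + 0.84√(p₁(1 − p₁) + p₂(1 − p₂))] / √441.3 with p₁ = 0.332, p₂ = p₁ − d, and p̄ their mean: d = 8.54 points

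The article states 8 points. The half-point gap does not affect this point.

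**4. Effect on precision.** The share of households meeting the rule is not given, so a range is assumed.

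| Share dropped (assumed) | Households of 1589 | Detectable difference |
|---|---|---|
| 0% | 0 | 8.54 |
| 0.5% | 8 | 8.55 |
| 1% | 16 | 8.56 |
| 2% | 32 | 8.59 |
| 5% | 79 | 8.66 |

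Even 5% moves it by only about 0.1 point.

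**5. Effect of selection.** Take a true prevalence p = 0.332 in both arms. If a fraction f is dropped and a proportion q of those dropped has poor well-being, the retained prevalence is (p − f·q)/(1 − f). The values of f and q are assumptions.
- Equal f and q in both arms: shift 0.
- q = 0.60, 1% against 2%: 0.3293 − 0.3265 = 0.003, or 0.3 point.
- q = 0.60, 1% against 3%: 0.3293 − 0.3237 = 0.006, or 0.6 point.
- q = 0.80, 1% against 3%: 0.3273 − 0.3175 = 0.010, or 1.0 point.

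The sign depends on which arm loses more. If the control arm does, its retained prevalence falls and a benefit is understated; if the intervention arm does, a benefit is overstated. The sums use the dichotomized outcome because the article gives its detectable difference on that scale. The planned analysis of mental well-being uses scale scores.

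**The case against.** A reader might infer that the rule breaks the stated intention-to-treat analysis. The documents do not support that. Kebeles are the randomized units, and none is dropped or moved. The rule does not depend on fidelity or compliance, which is all that the article's description sets aside, and it is the same in both arms. Nothing says that data from earlier rounds are discarded.

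A reader might also infer that losing the index child is enough to remove a household. The condition requires that no child in the window remains. If the 1385 index children with face observations are among the 1944 children aged 1–9 in Table 1, at least 1944 − 1385 = 559 other children in range were observed. Later births and infants at baseline can also enter the window. The rule is narrow.

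Nor do the documents show that the retained sample leans towards better well-being, or that loss differs by arm. Both are plausible, neither is demonstrated, and every rate in the selection sums is assumed.

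The rule also has a rationale. It keeps follow-up in the population defined at entry, and caregivers of index children are the main target audience. The 11 practices are detailed in a supplement not at hand, so how many need a child cannot be counted.

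All of this limits the size of the point. It does not explain why a willing adult should not be asked WHO-5 and HSCL, or why the household's latrine should not be observed. The intervention is also meant to change behavior among all household members and the wider community (Target audiences).

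**Conclusion.** The third condition is an avoidable post-randomization exclusion from adult mental well-being and from household and respondent outcomes that need no child. It departs from full follow-up of households in randomized clusters but leaves the intention-to-treat comparison, as described, in place. The issue is selection, not power: assumed losses of up to 5% move the detectable difference by about 0.1 point. The shift in the arm difference is 0 under equal loss, about 0.6 point at 1% against 3% with 60% poor well-being among those dropped, and about 1.0 point with 80%. The stated detectable difference is 8 points. The true rate and direction are unknown, and the number affected is probably small. The change is worth making because the loss is needless and its main triggers may be related to a primary outcome.

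**What to change.** Remove the third condition as a reason for household loss. Keep these households in follow-up for all respondent-level and household-level outcomes, and restrict only child-specific outcomes (face and hands, child feces, diarrhea) to households with an eligible child. Report the affected households by arm and round.

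For a round still to be collected, the cost is a wording change and a skip pattern for the child modules, plus the rest of the interview at a household already being visited. By the Timeline, endline was due to end in May 2019, and the article is dated 21 June 2019, so some or all rounds may already have been collected under the rule. For those, report losses under this condition by arm and round, and add a sensitivity analysis for mental well-being that varies the assumed outcome of the dropped respondents. That costs analysis time only.
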